#### Safety analyses

Analysis of safety endpoints will be performed in the safety analysis set. Adverse events will be analyzed as number and percentage per group. Events leading to a discontinuation of the intervention or withdrawal from the study will be tabulated.

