### Objectives

Against this background, the aim of this study is to evaluate the efficacy of PA in pwPCD. Based on clinical practice and experience from studies with pwCF [8–10], we assume a significant improvement in QoL as well as a slowing of disease progression through regular and, above all, mentored PA. This study shall close the evidence gap for PA as part of PCD therapy and lead to improved adherence to PA in pwPCD.

The main hypothesis of the trial is as follows: The support from an individualized and supported PA program results in higher PA and hence in a better quality of life 6 months after randomization (measured by physical functioning domain of QoL-PCD questionnaire) compared to treatment as usual in pwPCD with sole recommendation for PA (Table 1).

**Table 1 Tab1:** Objectives and endpoints

Objectives	Endpoints	Justification for endpoints
Primary		
To improve quality of life after 6 months of individual physical activity	Quality of life (physical functioning domain of the QoL-PCD questionnaire)	Well-established patient-relevant outcome
Secondary		
To evaluate the effect of the intervention on lung health, physical activity and fitness, as well as safety	Lung function parameters (VCmax (maximum vital capacity), FVC (forced vital capacity), FEV1 (forced expiratory volume in 1 s), PEF (maximum expiratory flow or peak flow), MEF 75/25 (maximum expiratory flow at 75/25% of FVC), sReff (specific airway resistance, if available), TLC (total lung capacity, if available)), Lung Clearance Index (LCI), if available	Relevant surrogates for health status and physical fitness of pwPCD with a chronic lung disease
	Physical fitness (motor test)	
	Physical activity (step count via activity tracker Garmin Vivo fit 4®)	Detection of the mechanism of action
	Quality of life (overall and single domains of the QoL-PCD questionnaire)	Detailed analysis of a well-established patient-relevant outcome
	Adverse events	Safety of intervention must be established

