To minimize the risks for participating patients, they are examined in detail for contraindications to participation in a PA program (see schedule of activities and “Exclusion criteria”) and receive comprehensive information when not to take part in PA. In addition, the focus of this study is on health-enhancing, individually adapted physical activity and not on physical exertion. The participants do the PA they prefer at their own pace under the close guidance of the qualified personal trainer. For this reason, the intervention group is questioned weekly by means of a standardized questionnaire about the occurrence of potentially critical complaints in the context of PA by the respective personal trainer. If one of the participants answers at least one of the questions in the lower third of the Numeric Analog Scale [1–4, 21, 29, 37, 40, 48, 49], which is handed out and explained at V0, PA will be discontinued immediately until medical clearance by the lead study center in Bochum is obtained. A standardized safety questionnaire must also be completed before the motor test that is part of the study visits. If there are indications of a medical concern, the lead study center Bochum will be contacted and if there is any doubt the test will not be performed.

An assessment of adverse events (AE) and serious adverse events (SAE) will be performed in the intervention and control group to evaluate the safety of the study intervention. For further details see below and under “Safety oversight.”

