#### Adverse events and serious adverse events

In the following, we define the AEs and SAEs to which we are limited in this study due to the chosen intervention and the clinical characteristics of PCD. They comprehensively recognize both the expected risks and serious complications.

Adverse event (AE)Any unplanned doctor contactPulmonary exacerbation or other pulmonary complications (obstruction, etc.)New antibioticsAccident during physical activity without hospital contactMedically justified discontinuation of physical activity (single occurrence)Discontinuation of intervention due to a medical cause

Serious adverse event (SAE)DeathAny unplanned hospitalization or hospital presentation

For adverse events (AEs), the following guidelines will be used to describe severity.Mild—Events require minimal or no treatment and do not interfere with the participant’s daily activities.Moderate—Events result in a low level of inconvenience or concern with therapeutic measures. Moderate events may cause some interference with functioning.Severe—Events interrupt a participant’s usual daily activity and may require systemic drug therapy or other treatment. Severe events are usually potentially life-threatening or incapacitating. Of note, the term “severe” does not necessarily have to be identical with “serious.”

All adverse events (AEs) will have their relationship to study procedures, including the intervention, assessed by appropriately trained clinicians (pediatric and internal medicine) based on temporal relationship and his/her clinical judgment. The degree of certainty about causality will be graded using the categories below.Related—The AE is known to occur with the study procedures, there is a reasonable possibility that the study procedures caused the AE, or there is a temporal relationship between the study procedures and the event. Reasonable possibility means that there is evidence to suggest a causal relationship between the study procedures and the AE.Not related—There is not a reasonable possibility that the study procedures caused the event, there is no temporal relationship between the study procedures and event onset, or an alternate etiology has been established.

During each study visit (V2–V4), a standardized query (CRF) is made by means of questionnaires of the AEs and SAEs defined above. In addition, all participants are encouraged to report unplanned hospitalizations (SAEs) to their supervising study center within 48 h.

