#### Populations for analyses

Three differing data sets are defined for the analyses:

Full analysis set

The full analysis set (FAS, based on the intention-to-treat (ITT) strategy) is defined to be all randomized patients according to their allocated intervention group, which fulfill the inclusion criteria and do not fulfill any exclusion criteria.

b)Per protocol set

The per protocol set (PPS) is defined by all patients belonging to the FAS without major violations of the study protocol. The following protocol violations are classified as major:Violation of an eligibility criterionDiscontinuation of intervention for non-medical reasonsNon-compliance

This is not an exclusive list. The full list of all major protocol violations, which will lead to the exclusion from the PPS, will be defined as part of the statistical analysis plan in the light of protocol violations which occur during study conduct. The final list of protocol violation will be finished before database closure and the beginning of the statistical analysis.c)Safety analysis dataset

The safety analysis set will include all randomized patients.

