#### Analysis of the secondary endpoint(s)

Analysis of all secondary outcomes will be done as complete case analysis, meaning that only cases with available data for the analysis are included. Analysis of the secondary efficacy outcomes will be undertaken following the same framework as the primary outcome model using appropriate generalized linear models.

For each continuous outcome, e.g., FEV1 and QoL-PCD, a linear regression model will be fitted, the intervention group, gender, FEV1 and the age group and the baseline value of the outcome considered were included as independent variables. For the QoL-PCD, an interaction term with age group is also added to the model.

For counting variables like number of pulmonary exacerbations, a similar generalized linear model will be fitted using a negative binomial distribution with a log link instead. Treatment effects are reported as relative risk with 95% confidence intervals.

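### Adverse events are tabulated per group although only the intervention arm is questioned weekly, and the stops this triggers are themselves adverse events

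*Protocol article*

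**What the plan says.** All references are to the protocol article.

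- **Purpose.** Table 1 under Objectives lists adverse events as a secondary endpoint because "Safety of intervention must be established". Safety assessments adds that their assessment "will be performed in the intervention and control group to evaluate the safety of the study intervention".
- **Analysis.** Safety analyses: "Adverse events will be analyzed as number and percentage per group". It also plans a table of events that led to stopping the intervention or leaving the study. Populations for analyses: "The safety analysis set will include all randomized patients".
- **Common ascertainment.** At V2, V3 and V4 (3, 6 and 12 months), "a standardized query (CRF) is made by means of questionnaires of the AEs and SAEs defined above" (Adverse events and serious adverse events). Between visits, all participants are asked to report unplanned hospitalisations within 48 hours.
- **Extra ascertainment in one arm.** Safety assessments: "the intervention group is questioned weekly by means of a standardized questionnaire about the occurrence of potentially critical complaints in the context of PA". An answer in the critical range halts activity until the lead centre gives medical clearance. The section on intervention discontinuation describes the consequence of a positive weekly answer as immediate discontinuation of the intervention.
- **Between-visit recording.** Sites must also notify events between visits, and every adverse event on study is to be documented.
- **Definitions.** The adverse event list contains "Discontinuation of intervention due to a medical cause" and, as a separate entry, a single medically justified stop of physical activity.

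**The concern.** A per-group table of counts and percentages shows relative harm only if events have a similar chance of being found and recorded in each arm. Here the chance differs by design. The control arm was deliberately not given the weekly contacts, which is a defensible choice for the efficacy question but leaves safety ascertainment unequal.

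There are two separate mechanisms. The first is detection: weekly questioning can bring to light events that a query after 3 or 6 months would miss. The second needs no assumption about recall. The safety procedure generates stops, the definitions make those stops adverse events, and the procedure runs in one arm only. Both mechanisms push the same way, towards apparent excess harm from a programme whose safety the trial is meant to establish. The same records go to the data and safety monitoring board once a year.

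**Working it through.** **1. Scheduled safety questioning per arm.** Weekly for 6 months is about 26 contacts. V2 and V3 fall within the first 6 months and V4 at month 12.

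| Period | Intervention | Control |
|---|---|---|
| First 6 months | 26 + 2 = 28 | 2 |
| 12 months | 26 + 3 = 29 | 3 |

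**2. Which adverse event categories depend on the arm.**

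- Stopping the intervention for a medical cause: impossible in controls, who have no intervention to stop.
- Medically justified stop of physical activity: possible in controls, who are also advised to be active and told when to stop. Between visits, however, it is actively looked for only in the intervention arm.
- The remaining categories (unplanned doctor contact, exacerbation, new antibiotics, accident) can occur in both arms and can differ only through detection.

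**3. Size of the category effect.** Assumption: a share q of the intervention arm has an event recorded only through these stops, independently of other events. The target of 158 gives 158 / 2 = 79 per arm.

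- q = 5%: 79 × 0.05 ≈ 4 participants. q = 30%: 79 × 0.30 ≈ 24. In controls there are none by this route.
- The any-event percentage rises by (1 − b) × q, where b is the percentage with another event. With b = 80% and q = 5% this is 0.20 × 5 = 1 point. With b = 40% and q = 30% it is 0.60 × 30 = 18 points.

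**4. Size of the detection effect.** The article gives no event rate and no capture probability, so all of these are assumptions: equal true rate of 1.5 events per person over 12 months, spread evenly (0.75 per half-year); 95% capture in the intervention arm in months 1 to 6; capture c in controls throughout and in both arms after month 6.

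Recorded events per person: intervention 0.75 × 0.95 + 0.75 × c; control 1.5 × c.

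| c | Intervention | Control | Ratio |
|---|---|---|---|
| 85% | 1.350 | 1.275 | 1.06 |
| 70% | 1.2375 | 1.050 | 1.18 |
| 50% | 1.0875 | 0.750 | 1.45 |

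At c = 70% and 79 per arm this is 79 × 1.2375 ≈ 98 recorded events against 79 × 1.05 ≈ 83, with no true difference.

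**5. Effect of a like-for-like comparison.** Restricting the comparison to the common query makes scheduled questioning 3 against 3 over 12 months instead of about 29 against 3.

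**The case against.** Several limits on the point are sound.

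- **No test is planned for adverse events.** A reader might infer a high chance of a statistically significant excess. Safety analyses is purely descriptive, so such a probability would describe a test that the plan does not contain.
- **The exacerbation count.** A reader might infer that the efficacy count of exacerbations is distorted as well. The section on secondary endpoints says "For counting variables like number of pulmonary exacerbations, a similar generalized linear model will be fitted" but names no data source. The exacerbation score and the V2 to V4 query are applied alike in both arms. Whether the count is affected depends on a source the article does not state.
- **Only one category is strictly impossible in controls**, and the planned table of events leading to discontinuation already shows part of this. It does not remove those events from the overall count.
- **The weekly questionnaire is not the adverse event form.** It asks about complaints during activity and reaches the adverse event data through stops and between-visit notification. It is not stated that a clearance by the lead centre counts as an unplanned doctor contact, so that route is not claimed here.
- **Weekly contact lasts 6 of the 12 months.** Applying 95% versus 70% to the whole year would give 0.95 / 0.70 = 1.36. The schedule supports the smaller 1.18 under the same assumptions.
- **Details of secondary endpoints are deferred to the analysis plan.** That plan can settle the tables, but it needs the source of each event to be recorded.

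What does not fall away is the main point. The article fixes the summary measure, the definitions and the unequal questioning, and together they bias the comparison in a known direction.

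**Conclusion.** The point holds as a matter of safety reporting. As written, the per-group counts and any-event percentages mix true risk with unequal ascertainment and will tend to overstate harm in the intervention arm. The direction follows from the article: one category is impossible in controls, and another is sought between visits in one arm only.

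The size cannot be derived from the article. The ratio of 1.18 (range 1.06 to 1.45 for control capture of 85% to 50%) and the 1 to 18 percentage points from stop-related categories rest wholly on the assumptions shown. Deaths and hospitalisations are much less affected, because every participant is asked to report hospitalisations promptly. The weekly safety questioning is not itself a fault.

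**What to change.** - Add a source field to the adverse event form: V2 to V4 query, or between-visit or weekly contact. Allow both, so that an event first noted in a call and reported again at the visit counts as elicited by the common query.
- Make the between-arm comparison on events elicited by the V2 to V4 query plus deaths and hospitalisations, and leave the intervention-only category out of its any-event total.
- Take the exacerbation count from the common V2 to V4 assessment in both arms, and say so.
- Keep the full all-source table by arm beside it, so that no harm is hidden. Show intervention-only and weekly-triggered events as a separate aggregate row; the article rules out tabulating individual data.
- State the unequal contact as a limitation. The source field reduces differential recall but does not remove it, because weekly calls may help participants remember events at the visit.

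The cost is one form field and one table. The field should be added while events are still being recorded, since the source may be hard to reconstruct later. Weekly safety questioning stays as it is.

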#### Baseline descriptive statistics

Demographic and baseline variables will be summarized in a table, stratified by treatment and control group. Continuous variables will be summarized using the arithmetic mean and standard deviation; in case of skewed distribution, median and interquartile range is used. Categorical variables will be summarized using total counts and percentages. No inferential statistics will be used to compare baseline characteristics.

#### Additional analyses

No tabulation of individual participant data will be done. No interim analysis will be performed. In addition, it is planned to conduct exploratory mediator analysis using the fitness tracker data to further investigate the mode of action of the intervention.

CCDC39/40 and CCNO gene variants in particular are associated with more rapid disease progression [50]. Participants with these mutations are therefore analyzed separately as a subgroup. Instead of further subgroup analyses, explorative moderator analyses are planned. Possible moderators for the intervention effect on change in quality of life are age group (children, adolescents, and adults), the motor test at baseline, genetic variant, and baseline FEV1. Moderator analyses will be performed using the model from the primary endpoint analysis with an additional inclusion of the treatment × moderator interaction.

### Data management and protection

In the study, personal data of the patients will only be processed in compliance with the relevant data protection regulations, i.e., only to the extent that this is necessary to conduct the study. The processing of patients’ personal data is only carried out after their verbal and written consent for data capture, transmission, and analysis. The patients are informed of this fact and agree to the procedure with the patient information/informed consent. Data captured by the investigators will be processed in such a way that it can be accurately reported, interpreted, and verified while the confidentiality of records and the personal data of the subjects remain protected. Data capture and processing will be in accordance with the applicable law on personal data protection and with the GDPR (EC) 2016/679 of the European parliament and of the council. Access to the data is strictly limited to authorized persons. Data are protected against unauthorized access. Study participant contact information will be securely stored at each clinical site for internal purposes and study evaluations, as well as for confidential use by the lead study center (e.g., contacting in the case of an SAE) or by the sports scientists (e.g., contacting for telephone interviews) during the study.

The investigators together with the trial sites are responsible for the implementation and data processing in accordance with Article 4(7) of the General Data Protection Regulation 2016/679 in this trial. The investigators are responsible for implementation of procedures for data collection, storage, protection, retention, and destruction. The database is hosted by the AMIB on servers, which are located at the RUB in access-protected server rooms.

Personal data collected for this study will be stored for 10 years from completion of the study. When the study is completed, access to study data will be provided upon request to the PI. All other data collected as part of this study will be analyzed and stored in a separate study database only with the pseudonymization number for at least 10 years after last publication. After the personal data has been deleted, the data is anonymized. Access to the final complete dataset is available to the study staff of the AMIB and the leading study center of the University Children’s Hospital Bochum as well as [name]. Study teams from other study centers will only have access to the complete dataset upon request and approval by the Publication Committee.

All data will be initially collected by investigators in the recruiting trial sites. Together with information on the trial, eligible patients will be informed about data capture, transmission, analysis processes, and their rights according to the General Data Protection Regulation (GDPR). Once a patient is eligible and has given his/her informed consent (concise version) to trial participation and data collection, the investigator will assign with the help of a separate “contact database” the patient a unique patient identification code which is generated by AMIB. The personal data and declarations of consent of the participants are stored in the separate contact database. These codes are part of the investigator site file. Re-identification of the patients is only possible with the help of the contact database. Access is only possible for authorized persons. The authorization levels depend on the function in the study. Study centers only see the subjects they have included. The leading study center and the training institute [name]. [name] (for the study period) will have access to all subjects to ensure scheduling, implementation of the intervention, and safety management.

All clinical data entered in the trial database by the investigators (or their designated staff) or patients into eCRFs will be recorded in a pseudonymized form exclusively using the patient’s identification code.

Patients may withdraw their informed consent. If patients withdraw their consent, no further data will be collected. However, the data processing carried out up to the date of withdrawal remains lawful. If the informed consent is withdrawn, the patient has the right of data deletion according to the GDPR. Information as to when and why a patient was randomized and when he withdrew consent must be retained in the documentation. According to GDPR, the institution responsible for conducting the study is generally obliged to delete its data from the study database after withdrawal of consent. According to the basic data protection regulation, the study participants have the following rights regarding their personal data:The right to be informed about their personal data that are collected, processed or, if applicable, transferred to third parties in the course of the clinical trial (if necessary, handing out a copy free of charge).Right to have incorrect personal data corrected. Right to have their personal data deleted, with the exception of the security data described above.Right to limit processing (in exceptional cases). The right to limit processing must be requested from the investigator or the data protection officer of the trial site.Right to data transfer of personal data collected about the study participant. This data shall be transmitted either to the trial participant himself or, if technically possible, to another body designated by the trial participant.Right to refuse (conditionally) the use of the data (see also right to cancelation).

